#### Secondary outcomes

General physical characteristics, including weight, height, BMI, abdominal circumference, body composition, heart rate, and blood pressure.Blood glucose-related indexes: HbA1c, FBG, PBG, fasting insulin, fasting C-peptide, 2-h postprandial insulin, and 2-h postprandial c-peptide levels; homeostasis model assessment of insulin resistance; and homeostasis model assessment of β-cell function.Related indexes of lipid metabolism: plasma levels of triglycerides, total cholesterol, low-density lipoprotein cholesterol, and high-density lipoprotein cholesterol.Complications-related indicators: eye-ground photography, electromyography, and color doppler ultrasound of blood vessels in the neck and lower limbs.Visceral fat content: abdominal ultrasonography.Intestinal flora.Metabolomics.

#### Safety outcomes

Participants will be followed up by telephone every month to inquire about their adverse reactions and events, and physical examinations, laboratory examinations as well as auxiliary detections will be conducted every three months. If there is a problem, take appropriate solutions and treatment measures, and record the situation in time.

Monitoring indexs: clinical symptoms; vital signs; electrocardiogram; blood and urine routine tests; liver and kidney functions; electrolyte levels; urinary albumin/creatinine ratio; myocardial enzyme profile; blood amylase level; thyroid function; eGFR; and blood/urine pregnancy test; and incidence of hypoglycemia, ketosis hypoglycemia and cardiovascular and cerebrovascular events.

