### Randomisation and interventions

A total of 184 participants will be randomly allocated to receive either canagliflozin or metformin treatment (1:1). The randomization operation will be generated by an independent statistician, who will ensure the balance of participants according to age, sex, HbA1c and BMI and course of their disease when grouping, and a code list will be directly allocated to the main investigators of every center. The intervention content of the two groups is as follows.

Canagliflozin treatment group: For oral treatment, the participants will receive canagliflozin tablets (Janssen-Cilag S.p.A., Ltd., National Drug Approval: H20170375) once daily, 100–300 mg per time, with a minimum dose of 100 mg per day and maximum dose of 300 mg per day.Metformin treatment group: For oral treatment, the participants will receive metformin hydrochloride tablets (Sino-American Shanghai Squibb Pharmaceutical Co., Ltd., National Drug Approval: H20023370 (0.5 g × 20 tablets)/Sino-American Shanghai Squibb Pharmaceutical Co., Ltd., National Drug Approval: H20023371 (0.85 g × 10 tablets × 2 plates)), 1–3 times a day, 500–2000 mg per time, with a minimum dose of 500 mg per day and maximum dose of 2550 mg per day.

Regarding weekly titration for oral drug metering, the titration targets are fasting blood glucose (FBG) (3.9–5.6 mmol/L) and blood glucose at 2 h after each of the three meals (5.0–7.0 mmol/L). After meeting the above criteria, the participants will continue the medication for 3 months and then stop.

Routine diabetes health education will be provided to all participants during the treatment period. Routine diet control and appropriate exercises will be planned. Follow-up will be conducted monthly for the first 3 months after the end of treatment and every 3 months thereafter for 1 year (Table 1; Fig. 2). Participants with FBG > 7.0 mmol/L and postprandial blood glucose (PBG) > 10 mmol/L during the follow-up period are defined as having hyperglycemia recurrence, which will be treated according to the Chinese guidelines for the diagnosis and treatment of T2DM and is defined as not remitted.

**Table 1 Tab1:** Participant visit schedule

**Research Stage**	**Screening**	**Baseline**	**Intervention Period**				**Follow-up Period**		

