			**Start of treatment**	**Dose titration period** **(weekly)**	**Maintenance treatment** **(monthly)**	**Drug discontinuance**	**First three months** **(monthly)**	**Last nine months** **(every three months)**	**End of the follow-up**
Informed consent		**×**	**×**	**×**	**×**	**×**	**×**	**×**	**×**
Participant information		**×**	**×**	**×**	**×**	**×**	**×**	**×**	**×**
Medical history		**×**	**×**	**×**	**×**	**×**	**×**	**×**	
Clinical examination		**×**	**×**	**×**	**×**	**×**	**×**	**×**	
Inclusion and exclusion criteria		**×**	**×**	**×**	**×**	**×**	**×**	**×**	**×**
Assignment filter number		**×**	**×**	**×**	**×**	**×**	**×**	**×**	**×**
Weight, height, and BMI									
Body composition	**×**		**×**	**×**	**×**		**×**	**×**	
Waist circumference									
Blood pressure and resting heart rate									
HbA1c, FPG, 2hPG			**×**	**×**	**×**		**×**		
FCP, 2hCP, FINS, INS-2 h	**×**		**×**	**×**	**×**		**×**		
Blood biochemistry, blood routine			**×**	**×**	**×**		**×**		
Thyroid function		**×**	**×**	**×**	**×**	**×**	**×**	**×**	**×**
Routine urine, urine microalbumin			**×**	**×**	**×**		**×**		
ECG, UCG		**×**	**×**	**×**	**×**	**×**	**×**	**×**	**×**
Abdominal ultrasonography	**×**		**×**	**×**	**×**	**×**	**×**	**×**	
Eye-ground photography, electromyography, color doppler ultrasound of blood vessels of the neck and lower limbs	**×**		**×**	**×**	**×**	**×**	**×**	**×**	
Stored samples (blood and stool)	**×**		**×**	**×**	**×**		**×**	**×**	
DSQLS、SDSCA	**×**		**×**	**×**	**×**		**×**	**×**	
Medication, diet, and exercise guidance	**×**								
Treatment of comorbidity	**×**								
Blood glucose monitoring	**×**	**×**							
Dietary and sport record	**×**	**×**							
Occurrence of hypoglycemia, ketosis, and other adverse reactions	**×**	**×**							
Distribute participant diaries		**×**	**×**	**×**	**×**	**×**	**×**	**×**	
Recall and review participant diaries	**×**	**×**	**×**	**×**	**×**	**×**	**×**	**×**	

BMI, body mass index; ECG, electrocardiograph; FCP, fasting C-peptide; FINS, fasting serum insulin; HbA1c, glycosylated hemoglobin A1c; 2hCP, 2 - hour postprandial C-peptide; INS-2 h, 2 - hour postprandial insulin; DSQLS, diabetes specific quality of life scale; SDSCA, summary of diabetes self care activities; UCG, ultrasonic cardiogram

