### Visits and measurements

#### Follow-up visit

At the beginning of treatment, participants will be required to visit the centre every week to report their blood glucose monitoring status, and receive adjustment of the dosage and frequency to achieve a fast and stable blood glucose standard. When the participant’s blood glucose level reaches the standard, the visit will be repeated every 2 ~ 4 weeks until the end of the treatment period. After drug withdrawal, participants will be followed up by telephone every month and return to the centre every 3 months until the end of follow-up.The specific follow-up items are shown in Table 1.

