#### Participant diary

Each participant will be provided a participant diary and instructed to record blood glucose, blood pressure, weight, abdominal circumference, medication, diet, exercise, and adverse reactions, such as hypoglycemia. We will check and record the participant’s diary during each follow-up and return visit.

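### Table 1 schedules ECG and thyroid function at screening only and leaves gaps in laboratory tests, clinical examination and diary review, contrary to the safety and diary text

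*Protocol article*

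**What the plan says.** **Safety outcomes.** Participants are telephoned monthly about adverse reactions, and "physical examinations, laboratory examinations as well as auxiliary detections will be conducted every three months". The monitoring list includes "electrocardiogram; blood and urine routine tests; liver and kidney functions; electrolyte levels; urinary albumin/creatinine ratio; myocardial enzyme profile; blood amylase level; thyroid function; eGFR". The section does not say whether the three-monthly rule covers treatment, post-treatment follow-up or both.

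**Follow-up visit.** Visits are weekly at first, then every 2 to 4 weeks once glucose is on target. "After drug withdrawal, participants will be followed up by telephone every month and return to the centre every 3 months". For what is done at each contact, sites are told: "The specific follow-up items are shown in Table 1".

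**Participant diary.** Diaries hold glucose values and adverse reactions such as hypoglycaemia. Staff are to check and record the participant's "diary during each follow-up and return visit".

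**Randomisation and interventions.** Doses are titrated weekly with no stated maximum duration. Once targets are met, "the participants will continue the medication for 3 months and then stop". Follow-up is then monthly for three months and three-monthly up to one year. Table 1 sets this out in nine columns and includes the rows "Blood biochemistry, blood routine" and "Recall and review participant diaries".

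**Data analysis.** Safety indicators are to be analysed by the methods used for the main outcome, that is, as a comparison between the two arms.

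**The concern.** The visit schedule is what sites work from, and here the text explicitly delegates to it. If Table 1 leaves closed what the safety section promises, listed safety indexes will not be collected. An index with only a screening value says nothing about either drug and cannot be compared between arms, whatever test is planned. Two sites could also act differently in good faith, one following the text and the other the table, which would make missing safety data depend on centre.

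**Working it through.** There is no plan figure to reproduce. The check reads each Table 1 row cell by cell and sets it beside the text.

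**Step 1: meaning of ×.** No legend is visible, so the meaning has to come from rows with only one sensible reading.
- Informed consent has × in every column except screening.
- Weight/height/BMI and blood pressure/heart rate have no × at all.
- Hypoglycaemia and other adverse reactions have × only at screening and baseline.
- HbA1c, an entry criterion and the basis of the primary outcome, is blank at screening and at end of follow-up.

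All four fit × = 'not done'. With × = 'done', consent would be taken everywhere but screening, blood pressure would never be measured, adverse reactions would be recorded only before treatment, and HbA1c would be absent at screening and at the end. That reading would also conflict with the safety text.

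**Step 2: open columns.** The nine columns are (1) screening, (2) baseline, (3) start of treatment, (4) titration, (5) maintenance, (6) drug discontinuance, (7) first three months, (8) last nine months, (9) end of follow-up. Columns 3 to 6 form the intervention period.

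| Row | × in columns | Open columns | Open count |
|---|---|---|---|
| ECG, UCG | 2–9 | 1 | 1 of 9; 0 of 8 after screening |
| Thyroid function | 2–9 | 1 | 1 of 9; 0 of 8 after screening |
| Clinical examination | 2–8 | 1, 9 | 2 of 9 |
| Biochemistry, blood routine | 3, 4, 5, 7 | 1, 2, 6, 8, 9 | 5 of 9; 1 of 4 in the intervention period |
| Urine | 3, 4, 5, 7 | 1, 2, 6, 8, 9 | 5 of 9; 1 of 4 in the intervention period |
| Diary recall and review | 1–8 | 9 | 1 of 9 |
| Hypoglycaemia, ketosis, adverse reactions | 1, 2 | 3–9 | 7 of 9 |
| Blood pressure, heart rate | none | 1–9 | 9 of 9 |

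**Step 3: narrowest reading of the three-monthly rule (follow-up only).** Over 12 months it gives 12 / 3 = 4 occasions: months 3, 6, 9 and 12. Month 3 falls in column 7; months 6, 9 and 12 fall in columns 8 and 9.
- ECG/UCG and thyroid function: 0 of 4 open.
- Clinical examination: 1 of 4 open (the end).
- Biochemistry, blood routine and urine: 3 of 4 open; month 3 is closed.

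**Step 4: wider reading (treatment as well).** Time on drug is T + 3 months, where T is the titration time. For any T > 0 this exceeds three months, so at least one laboratory occasion would fall due before drug discontinuance. Table 1 has none between baseline and that visit. The length of the gap cannot be computed, because T has no stated limit.

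**Step 5: diary.** The text has the diary checked at every follow-up and return visit; the table opens recall and review in column 9 only.

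Electrolytes, myocardial enzymes, amylase, and liver and kidney function have no rows of their own. I have assumed that they belong to the biochemistry row.

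**The case against.** A reader might infer that renal, hepatic and cardiac safety would go unmeasured for the whole time on drug. The table does not support that. Biochemistry, blood routine and urine are open at baseline and at drug discontinuance, the last column of the intervention period, so a before-and-after comparison exists in both arms. Blood pressure and heart rate are open at every visit.

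A reader might also infer that hypoglycaemia would surface only when diaries are reviewed at the end. That does not hold either. The rows for adverse reactions and for blood glucose monitoring are open from start of treatment, and participants report glucose at the weekly titration visits.

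The three-monthly rule may not apply on drug. The safety section describes monthly calls and three-monthly examinations, which is exactly the pattern the Follow-up visit section gives for the time after withdrawal. This stands: the on-drug laboratory conflict is possible but not established. It does not rescue ECG, thyroid function or clinical examination, which fail the rule in follow-up as well. The closed laboratory cells in the first three months are partly explained by the monthly contacts being telephone calls, but month 3 is also a centre visit.

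Diary recall and review could mean final collection, with checking at each visit left to the text. That is possible, and it makes the diary conflict the softest of the four.

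Finally, the table was read by a program, without a legend, and supplementary material is not shown. The chosen reading is not free of oddities: it has diaries distributed at screening and again at end of follow-up. The counts therefore depend on the inferred meaning of ×. The opposite meaning is much less plausible and would not remove the disagreement with the text.

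**Conclusion.** The point holds as a contradiction between Table 1 and the text.

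- **Firm, on either reading of the three-monthly rule:** ECG/UCG and thyroid function are scheduled at screening only (0 of 8 later columns), and clinical examination at screening and end of follow-up only. For ECG and thyroid function, both listed safety indexes, a site following the table would have no post-randomisation data, and the planned between-arm comparison could not be made.
- **Smaller:** biochemistry, blood routine and urine are closed in the column that contains the month-3 visit.
- **Unclear:** whether laboratory tests are also required between baseline and drug discontinuance. Table 1 has none there, and the text does not say which period its rule covers.
- **Softest:** diary review is open in 1 of 9 columns, against a text that has it at every visit.

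The conclusion assumes that × means 'not done' and that the table was extracted correctly. It concerns the safety data and does not show that renal, hepatic or hypoglycaemia data would be absent.

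**What to change.** The sponsor should reconcile Table 1 with the Safety outcomes, Follow-up visit and Participant diary sections and state which governs. Specifically:

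1. State whether the three-monthly rule covers the treatment period, the follow-up period or both.
2. Make the table and the list of safety indexes agree, so that each listed index either has scheduled post-baseline measurements or is removed from the list.
3. Say what the diary row means, and align it with the diary text.
4. If the published table has no key to ×, add one.

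Which tests are done and when is for the sponsor to decide; no schedule is proposed here.

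The cost is a table correction. The visits already exist and the examinations are already promised in the text, so the only added burden is some routine tests at sites that had planned from Table 1.

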#### Life quality outcomes

Diabetes specific quality of life scale (DSQLS) and summary of diabetes self care activities (SDSCA) will be used to assess life quality outcomes.

#### Compliance outcomes

The compliance outcomes include the implementation rates of various examinations, medications, and diet, compliance with exercise, return visit rate, and follow-up evaluation.

### Visits and measurements

#### Follow-up visit

At the beginning of treatment, participants will be required to visit the centre every week to report their blood glucose monitoring status, and receive adjustment of the dosage and frequency to achieve a fast and stable blood glucose standard. When the participant’s blood glucose level reaches the standard, the visit will be repeated every 2 ~ 4 weeks until the end of the treatment period. After drug withdrawal, participants will be followed up by telephone every month and return to the centre every 3 months until the end of follow-up.The specific follow-up items are shown in Table 1.

#### Anthropometric measures

Anthropometric measurements will be performed at each research center by trained surveyors using standardized operating procedures. The participants will be instructed to remove their shoes and heavy clothes when measuring their weight; height and waist circumference will be measured in centimeters using a unified measuring instrument. The attending physicians will ask and record the participants’ clinical symptoms, perform physical examinations, and guide them to complete the DSQLS and SDSCA.

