## Methods and analysis

### Study design

This is a multicenter, parallel-group, randomized controlled, open-label trial (Fig. 1). The study has been approved by the Medical Ethics Committee of the Jiangsu Hospital of Integrated Traditional Chinese and Western Medicine and registered in the Chinese Clinical Trial Registry (ChiCTR2100043770). This study will be conducted at Jiangsu Hospital of Integrated Traditional Chinese and Western Medicine, Suzhou Hospital of Traditional Chinese Medicine, Suqian Hospital affiliated with Xuzhou Medical University, Xuzhou Mineral Group General Hospital, Xiamen Hospital of Traditional Chinese Medicine, and Nanjing Jiangning District People’s Hospital. A total of 184 participants will be enrolled and randomly assigned to the canagliflozin and metformin treatment groups.

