### Outcomes

#### Primary outcome

Remission rates.

This is the percentage of participants in each group who meet the remission criteria during follow-up: HbA1c < 6.5% maintained for > 3 months after the treatment discontinuation [27].

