### Data analysis

All statistical analyses will be performed by full-time statisticians using R Studio (Version 1.2.5001, R Studio Inc., Boston, MA, USA). The normality test will be used to determine whether the data are normally distributed. Continuous variables with a normal distribution will be reported as the mean ± SD, and ordinal and non-normally distributed variables will be reported as the median and interquartile range. Independent samples t-tests or Mann-Whitney U-tests will be used for comparisons, as appropriate. Categorical variables will be reported as counts and proportions, and the Pearson χ^2^ test or Fisher’s exact test will be used for comparisons, as appropriate.

The primary outcomes (remission rate 3 months after drug withdrawal and after 1 year of follow-up) will be compared between groups using Pearson’s χ^2^ test or Fisher’s exact test. Logistic regression will be used to adjust for potential confounders. Variables with P < 0.05 in the univariate comparisons, and known confounders that could impact the efficacy, will be included in the multivariable logistic regression models.

Subgroup analyses will be conducted of the primary outcomes stratified by age group (young, 18 ~ 35 years; middle-aged, 36 ~ 59 years; older, 60 ~ 65 years); duration of disease (<1 year, 1 ~ 2 years, 2 ~ 3 years); BMI (18.5 ~ 27.9 kg/m^2^, 28 ~ 40 kg/m^2^); and sex, using the same methods of analysis.

For the secondary outcomes, continuous data will be analyzed using the linear mixed effects model, which will use the random intercept model to explain the internal correlation of participants. Discontinuous data will be analyzed similar, but the generalized linear model appropriate to the distribution assumptions and link functions will be used. The analysis of all secondary outcome indicators also corrected for potential confounders (including variables with P < 0.05 in the univariate comparisons and known confounders that could have an impact on the efficacy). The safety indicators will be analyzed using the same methods used to analyze the main outcome indicators.

Missing values will be filled using multiple imputation methods, and sensitivity analyses will be performed.

Two-tailed P-values will be used, and P-values < 0.05 will be regarded as statistically significant. Point estimates will be reported with 95% confidence intervals.

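### Attending physicians guide completion of the two quality-of-life scales in an open-label trial, an avoidable route for influence that could differ by arm (minor)

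*Protocol article*

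**What the plan says.** Four places in the protocol article bear on this point.

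- **Anthropometric measures** (under Visits and measurements): "The attending physicians will ask and record the participants’ clinical symptoms, perform physical examinations, and guide them to complete the DSQLS and SDSCA". The same paragraph gives the body measurements to trained surveyors who follow standardized procedures.
- **Life quality outcomes**: the DSQLS and SDSCA are the only instruments named, and they "will be used to assess life quality outcomes". They are trial outcomes, listed apart from the primary and secondary outcomes.
- **Study design**: "This is a multicenter, parallel-group, randomized controlled, open-label trial".
- **Randomisation and interventions**: "a code list will be directly allocated to the main investigators of every center".

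The article mentions no blinded or independent questionnaire administrator and no unassisted completion.

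**The concern.** Both scales record what the participant reports. The help given while answering is part of the measurement. Here that help comes from the attending physician, in a trial where the drug is known to everyone. If the physician's view of the assigned drug colours how an item is explained or which answer seems acceptable, the scores can move. If the movement differs between canagliflozin and metformin, it appears in the results as a drug effect on quality of life or self-care.

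The models in Data analysis cannot repair this. Confounder adjustment and multiple imputation deal with other problems, and a reporting shift that runs along the arms cannot be told apart from a treatment effect. It has to be prevented when the data are collected.

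This is a procedure that the article states, so it is not a detail merely left to a fuller document. The assignment also looks the wrong way round: the more objective body measurements get dedicated, standardized assessors, while the more suggestible outcomes are guided by the treating clinician.

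**Working it through.** The article gives no figure on this point, so there is nothing to reproduce. The check has two parts.

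**1. Does the text support the exposure?**

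- *Who helps:* the attending physicians (Anthropometric measures).
- *What they can know:* the design is open-label (Study design), and the allocation list goes to the main investigators at each center (Randomisation and interventions). Doses are adjusted at visits (Follow-up visit). No section keeps the attending physicians apart from staff who know the arm.
- *What is affected:* the two named life quality instruments (Life quality outcomes).
- *What is not affected:* the primary outcome, "HbA1c < 6.5% maintained for > 3 months after the treatment discontinuation", which is a laboratory measure.

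The route for influence exists on the text as written. The text says nothing on whether it is used, or used differently by arm.

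**2. What would a differential shift do?** (illustration only)

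Inputs:

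- Two-sided level 0.05, from Data analysis: "Two-tailed P-values will be used, and P-values < 0.05 will be regarded as statistically significant".
- 92 enrolled or 73 evaluable per arm, from Sample size calculation.
- Differential shift *b*, in SD units: **assumed**, because the article gives none. The range shown is 0 to 0.3.

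For two means with equal arms and no true effect, by the normal approximation:

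SE = √(2/n)

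P(reject) = Φ(b/SE − 1.96) + Φ(−b/SE − 1.96)

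For n = 92, SE = √(2/92) = 0.147. With b = 0.2, b/SE = 1.357, so P = Φ(−0.603) + Φ(−3.317) = 0.274.

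For n = 73, SE = √(2/73) = 0.166. With b = 0.2, b/SE = 1.208, so P = Φ(−0.752) + Φ(−3.168) = 0.227.

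| Assumed shift b (SD) | P(reject), 92 per arm | P(reject), 73 per arm |
|---|---|---|
| 0 | 0.050 | 0.050 |
| 0.1 | 0.104 | 0.093 |
| 0.2 | 0.274 | 0.227 |
| 0.3 | 0.530 | 0.441 |

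The first row matters as much as the last: without a differential shift the level is intact. The table takes *b* as the whole shift between arms. It does not divide *b* into a part from the physician and a part from participants knowing their own drug.

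**The case against.** The case on the other side has real weight, and most of it limits the point.

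- *Guiding is not interviewing.* The participants complete the scales, and guidance may mean no more than explaining the form. This stands. A reader might infer interviewer bias, with answers drawn out by the physician, but the article does not say so.
- *Wanting to please the physician would occur in both arms.* A reader might infer that the SDSCA is especially exposed because participants report their self-care to the person who advised them. Education, diet control and exercise are planned for all participants, so such over-reporting need not bias the comparison. The article also does not say who gives the advice, and it does not show the SDSCA items. This stands.
- *No stated expectation on these scales.* A reader might infer from the Background that the team expects canagliflozin to win. The hypothesis there is that canagliflozin could be effective for remission. It makes no comparison with metformin on quality of life or self-care. Study objectives poses superiority as a question, and Sample size calculation assumes equal remission rates. This stands.
- *The fix leaves participants unblinded.* True. Self-completion removes only what the physician adds.
- *The illustrated error rates are driven by assumed shifts.* True. They cannot be read as errors that the fix would prevent.
- *It is a design preference, and the article is condensed.* This does not fully stand. The article fixes who guides the questionnaires, no other section offsets it, and a safer arrangement is available at almost no cost.

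**Conclusion.** The point holds in a limited form. In an open-label trial, physicians who are not separated from knowledge of the allocation guide completion of the only two named life quality instruments. That leaves the DSQLS and SDSCA open to an avoidable influence that could differ by arm.

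The article shows exposure, not bias, and gives no basis for its size. Two things are assumed: that attending physician carries its ordinary meaning of a treating clinician, and that guidance may go beyond handing over and explaining the form.

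A reader might infer that the trial's main conclusion is at risk. It is not: remission rests on HbA1c, and the stated objectives concern remission and mechanism, so none depends on these scales. Severity is minor.

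**What to change.** In Anthropometric measures, remove the questionnaires from the attending physicians' tasks and state instead that:

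- participants complete the DSQLS and SDSCA themselves, before the consultation;
- where reading help is needed, site staff who do not treat the participant give it in neutral wording, for example the trained surveyors already named there.

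When these outcomes are reported, acknowledge that participants knew their drug, because this change does not remove their own reporting bias.

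The cost is one clause and a change in the order of steps at the visit. No new procedure is needed. No extra staff are needed either, provided the surveyors or similar staff can give occasional help; the article currently assigns the surveyors only body measurements. The downside is a few more unanswered items without guidance. By the article's own dates (publication in October 2023, recruitment from December 2023), the change could have been made before any questionnaire was collected.
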